### 9.4.3 Analysis of the Secondary Endpoint(s)

To account for inter-patient heterogeneity, our primary comparison will be to use a difference in differences analysis to examine change from their own baseline after 8 weeks of treatment with dronabinol. Comparisons of changes in WBC with differential, CRP, tryptase, substance P, and cytokines from baseline to end of study between patients on placebo and dronabinol will be done using t-tests or Wilcoxon rank-sum tests. A backward stepwise multivariate regression analysis will be performed to assess for covariates associated with the primary and secondary outcomes. As the group size will be small a regression analysis will also be done to assess if any covariates associated with the outcomes are significantly difference between the study groups.

### 9.4.4 Safety Analyses

Patients with SCD will be expected to have laboratory abnormalities and diagnoses of clinical or psychiatric conditions at baseline.  Comparison will be of new adverse events, complaints, or diagnosis in those on dronabinol to those on placebo.  The number and the percentages of patients experiencing new adverse events will be tabulated by study arm. Comparisons will be made using Fisher’s exact tests for each individual adverse event reported when appropriate.

### 9.4.5 Baseline Descriptive Statistics

Intervention groups will be compared on baseline characteristics, including demographics and laboratory measurements, using descriptive statistics.

Though we expect to balance important potential confounders of prior history of cannabis use and neuropathic pain between the two groups via randomization, we will examine whether these differ by randomization group and baseline or over the intervention period. If there are differences between groups, we will include these variables in models.

### 9.4.6 Planned Interim Analyses

Interim analyses of the data will be conducted when 50% of the sample has accrued. If the results show overwhelming, statistically significant differences in pain impactor opioid use between groups, the study will be stopped. If we find that serious adverse events are significantly more likely in the intervention arm the study will be stopped.

Interim analyses will be conducted by the biostatistician. [name] will review all pertinent data to determine whether to continue accrual. A decision to stop the study may be made at any time that the research team and DSMC agree that an unacceptable type and/or frequency of adverse events has been observed. [name] will report the decision to terminate the study to the DSMC and IRB within 48 hours of this determination. He will submit a narrative description of the reasons for early termination of the study to the IRB within 10 days.

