## 9.2 Sample Size Determination

In a study examining the responsiveness of PROMIS pain impact to changes in chronic pain patients who stated pain was a “little better” had an average increase of 1.8 point with a SD of 6.6 points and “much better” was associated with an average increase of 6.8 points with a SD of 6.5 points.^65^  Based on this we have chosen a change of 5 points as representing a clinically meaningful improvement in chronic pain, with an estimated a SD of 6.5 points. With a sample size of 28 patients (56 total) in each group we will have 80% power to detect a difference of 5 points in change between two groups in pain impact score from baseline at a two-sided 0.05 significance level.

We have a strong track record of following subjects with chronic pain, opioid use, and SCD in ourprior SCD studies have achieved 85-100% retention at 6 months. In our pilot trial we approached 27 patients to enroll 6 on study, we therefore estimate if we approach 280 patients, we can enroll 70. We conservatively estimate a 20% attrition rate, so we will aim to approach 280 patients to enroll 70 to ensure 56 participants completing the study.

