## 9.4 Statistical Analyses

### 9.4.1 General Approach

We will first conduct descriptive and graphical analyses to check for outlier and abnormal values, verify that distribution of measures meets assumptions of planned statistical tests, and explore the success of randomization. Primary analyses for all aims will be intent-to-treat analyses of data from baseline to week 8, based on group allocation. Secondary analysis will be done removing patients who do not complete at least 4 weeks on study as well as any patients whose urine samples show presence of cannabinoid metabolites other than THC or whose pill counts reveal they took less than 50% of the reported optimized dose.

Statistical analysis will be done assuming all data is non-normal. Continuous data will be described as means and quartiles, categorical data will be described as percentages.  All inferential tests will be two-tailed.

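### The half-way efficacy stop has no numeric boundary and can be triggered by a secondary endpoint, so the two-sided 0.05 level is not guaranteed

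*Protocol*

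**What the plan says.** Protocol section 9.4.6 sets the timing: "Interim analyses of the data will be conducted when 50% of the sample has accrued". It then gives the efficacy rule: "If the results show overwhelming, statistically significant differences in pain impactor opioid use between groups, the study will be stopped". The missing space is a typing slip; the sentence names pain impact or opioid use.

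The two endpoints differ in rank. Section 3 makes the PROMIS pain impact score the primary outcome. Sections 3 and 6.5 list change in opioid use as secondary.

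Section 9.2 plans a single analysis "at a two-sided 0.05 significance level": "With a sample size of 28 patients (56 total) in each group we will have 80% power". It does not mention an interim look. Section 9.4.1 adds: "All inferential tests will be two-tailed". Section 9.4.2 compares the change from baseline by a rank-sum test at the end and gives no reduced final level.

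On who decides, section 9.4.6 says that the biostatistician runs the interim analysis and that a person whose name is removed "will review all pertinent data to determine whether to continue accrual". A later sentence says that a person whose name is also removed "will report the decision to terminate the study to the DSMC and IRB within 48 hours".

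**The concern.** The rule is mandatory: if the condition is met, the study stops. But the condition rests on an adjective. *Overwhelming* points to something stricter than ordinary significance, but no number is attached here or elsewhere in the protocol. Whoever applies the rule must choose the threshold, possibly after seeing the data. Meanwhile the whole 0.05 is already committed to the final test, so any additional chance to declare success at the look adds to the error.

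The second problem does not depend on the threshold. Opioid use can end the trial by itself, but the sample size was worked out for pain impact only. A stop on opioid use would leave the primary question with roughly half its data. Section 2.3.3 says that a finding of efficacy would lead to a phase III proposal, so an early stop on a secondary measure would have consequences.

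**Working it through.** **Step 1: the plan's own figure.** Section 9.2 gives a difference of 5 points, SD 6.5, two-sided 0.05 and 80% power.

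- Normal approximation: n per arm = 2 × (1.960 + 0.842)² × 6.5² / 5² = 26.5, so 27.
- Two-sample t-test: 27.5, so 28 per arm, with power 80.7%.
- Attrition of 20%: 56 / 0.8 = 70 enrolled.

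The stated 28 per group, 56 completing and 70 enrolled are reproduced. They are fixed-design figures at the full 0.05.

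**Step 2: assumptions the protocol does not supply.**

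- Information fraction 0.5 at the look (28 of 56 with week-8 data), so the correlation between interim and final statistics for one endpoint is √0.5 = 0.707.
- Correlation r between the pain impact and opioid statistics, varied from 0 to 0.9.
- Final test on pain impact at |z| > 1.960.
- The interim threshold, varied because the protocol gives none.

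**Step 3: nominal p<0.05 at the look.** Under the null, error = 1 − P(no statistic crosses), from the multivariate normal distribution.

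- Pain impact at both looks: 8.3%.
- Either endpoint at the look, then pain impact at the end:

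| r | 0 | 0.3 | 0.5 | 0.7 | 0.9 |
|---|---|---|---|---|---|
| Error | 12.9% | 12.6% | 12.2% | 11.4% | 10.1% |

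A simulation with rank-sum tests at 14 and 28 per arm (40,000 runs for each r) gave 13.0%, 12.7% and 11.8% at r = 0, 0.3 and 0.5. The result is therefore not an artefact of the normal approximation.

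**Step 4: stricter readings of *overwhelming*, final test still at 0.05.**

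| Interim threshold | Pain impact alone | Either endpoint at the look (r = 0 to 0.5) |
|---|---|---|
| p<0.01 | 5.5% | 6.3-6.4% |
| p<0.005 | 5.2% | 5.6-5.7% |
| p<0.001 | 5.02% | about 5.1% |

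**Step 5: boundaries that hold 0.05 for pain impact alone (interim, then final).**

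- Haybittle-Peto: 0.001, then 0.0498.
- Lan-DeMets O'Brien-Fleming: about 0.003, then 0.049.
- Classical O'Brien-Fleming: 0.0052, then 0.0480.
- Pocock: 0.0294 at both.

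None of these covers opioid use as a further trigger.

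**Step 6: power cost.** With 28 per arm, the SE of the difference is 6.5 × √(2/28) = 1.737, and 5 / 1.737 = 2.878. Power of the final test is Φ(2.878 − 1.960) = 82.1% at 0.05 and Φ(2.878 − 1.969) = 81.8% at 0.049 (normal approximation).

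**Step 7: timing.** Section 5.5 expects 2-3 enrolments a month and treatment lasts 8 weeks, about two months. About 4-6 of those accrued would lack week-8 data at the look. The text also does not say whether half the sample means 28 of 56 or 35 of 70.

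**The case against.** The strongest reply is that the rule asks for more than significance. A reader might infer that the trial's error is 12-13% as the plan is written. The protocol does not support that. The figure requires *overwhelming* to be ignored, the endpoint correlation to be about 0.5 or less, and a stop on opioid use to count as a false positive. The 0.05 in section 9.2 belongs to the pain impact comparison only, and there the error is at most 8.3% at information fraction 0.5. With p<0.001 at the look it would be 5.02%, which is the stated level for practical purposes. A final test at about 0.05 is therefore not itself the fault; the missing boundary is. This part of the reply stands.

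A statistical analysis plan that is not shown might give the number. That would settle the threshold, but the opioid-use trigger is written into the protocol and would remain.

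Two other inferences are tempting and should be held back.

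- **Unblinded results held outside the DSMC.** The reviewing person's role is removed from the text. The 48-hour sentence follows one about stopping for adverse events by agreement of the research team and the DSMC. The protocol does not say that results are shown by arm to the investigators. What can be said is that section 9.4.6 gives the DSMC no stated part in an efficacy decision, while section 6.3 commits to double blinding.
- **A gross overestimate after an early stop.** With 14 per arm, SE = 6.5 × √(2/14) = 2.46, and nominal significance needs 1.96 × 2.46 = 4.8 points (about 5 by the t-test). The mean estimate among favourable stops is 6.1 if the true effect is 2.5 points, but 6.8 if it is the design value of 5. The size of the exaggeration depends on the effect chosen. A stricter boundary makes such stops rarer, but does not remove the bias when one occurs.

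**Conclusion.** The concern holds in this form: section 9.4.6 obliges the trial to stop on either of two endpoints without a numeric boundary, while section 9.2 commits the full two-sided 0.05 to a design with no look, so that level is not guaranteed.

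Across the thresholds tried, the error for pain impact runs from 5.02% to 8.3%, and for either endpoint from about 5.1% to 13%. Both ranges assume an information fraction of 0.5 and a final test at 0.05. The top of the second also needs nominal 0.05 at the look and endpoint correlation near zero. The width of these ranges comes mainly from one undefined word.

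Independently of the threshold, a secondary endpoint for which the trial was not sized can end it with about half the planned primary data. This is the firmest part of the point. The accrual-based timing and the unclear reporting route are minor additions.

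**What to change.** Amend section 9.4.6, and align section 9.2 with it:

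1. Remove opioid use as an efficacy stopping trigger and keep it as a secondary endpoint.
2. Allow an efficacy stop on pain impact only, at a stated boundary: Haybittle-Peto, p<0.001 at the look and about 0.05 at the end (0.0498 exactly), or Lan-DeMets O'Brien-Fleming, about p<0.003 and then 0.049. Give the final level in section 9.2.
3. Hold the look when 28 of the 56 planned completers have week-8 data.
4. State that between-arm interim results go to the DSMC, which recommends whether to continue.

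No additional participants are needed. Power of the final test falls by about 0.3 percentage points at most (82.1% to 81.8%). Early efficacy stops become rarer: with 14 per arm, p<0.001 needs an observed difference of about 3.29 × 2.46 = 8.1 points.

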## 6.2 Preparation/Handling/Storage/Accountability

### 6.2.1 Acquisition and accountability

### 6.2.2 Formulation, Appearance, Packaging, and Labeling

### 6.2.3 Product Storage and Stability

### 6.2.4 Preparation

## 6.3 Measures to Minimize Bias: Randomization and Blinding

The study will be double blind, neither investigators or subjects will know whether subjects are receiving dronabinol or placebo during either dosing period. To protect this blinding study team personnel will not be aware of the results of the urinary toxicology done after randomization. Study team personnel and subjects will be aware that subjects will take dronabinol 5 mg capsules or placebo, but they will not know which dosing period involves dronabinol or placebo.

Study group assignment procedures, and rationale for intervention’s dose, frequency and administration.

Subjects meeting all eligibility criteria will be randomized to dronabinol or placebo for 8 weeks.  We will randomize in a 1:1 ratio, via central, computer-generated randomization done by the pharmacy, stratified by history of prior cannabis use (yes or no) and presence of neuropathic pain (yes or no). To minimize bias in treatment group allocation, the data manager will store the allocation sequence using a password-protected file and has no contact with study participants. We will use urn randomization to minimize risks of imbalance in treatment allocation.

Neuropathic pain will be defined by Leeds Assessment of Neuropathic Signs and Symptoms (LANSS) (score >12). Past-year cannabis use will be defined by self-report of any cannabinoid use (medical, illicit, or cannabidiol containing (CBD) products) in the past year. Based on our prior experience as well as the experience of others, we expect 50% to have neuropathic pain and 50% to have past-year cannabis use after excluding frequent cannabis users.

Capsules of generic dronabinol will be over-encapsulated with methylcellulose filler in between the capsules and placebo will be formulated with matching cellulose capsules filled with methylcellulose. Matching labels for dronabinol and placebo bottles will be provided.

Encapsulated Dronabinol Capsules

For blinding, one intact active dronabinol capsule will be placed in a capsule shell, back filled with sufficient quantity of microcrystalline cellulose, and closed. The capsules are visually inspected and packed into Polypropylene bottles .

Placebo for Encapsulated Dronabinol Capsules

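### Section 9.4.6 gives the interim accrual decision to a named party, apparently not the DSMC, and sets no barrier between the comparative results and the masked study team

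*Protocol*

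**What the plan says.** Protocol section 9.4.6 sets the look: "Interim analyses of the data will be conducted when 50% of the sample has accrued". It gives two stopping rules. For efficacy: "If the results show overwhelming, statistically significant differences in pain impactor opioid use between groups, the study will be stopped". For safety: "If we find that serious adverse events are significantly more likely in the intervention arm the study will be stopped".

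On who does what, the section says "Interim analyses will be conducted by the biostatistician". A named party (name removed) then "will review all pertinent data to determine whether to continue accrual". A named party also "will report the decision to terminate the study to the DSMC and IRB within 48 hours of this determination". Between these two sentences stands a second route, for an unacceptable type or frequency of adverse events: "A decision to stop the study may be made at any time that the research team and DSMC agree".

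Section 6.3 commits that "neither investigators or subjects will know whether subjects are receiving dronabinol or placebo during either dosing period", and keeps toxicology results obtained after randomization from study personnel. Section 8.1 adds that those results stay unread until the participant has finished, for the sake of the mask.

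**The concern.** In a double-masked trial, comparative interim results normally go to a body that has no contact with participants. Here a DSMC exists: sections 5.5 and 7.3 send it reports every 6 months, and section 8.3.5 sends it serious adverse events. Yet section 9.4.6 does not ask it to review the interim efficacy comparison or to recommend on it. The decision lies elsewhere, and no wall is described around the results.

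What is at stake is operational bias after the look. The primary endpoint is a patient-reported pain score (section 3). Study clinicians agree the dose with each participant, including later upward changes (section 6.1.2). The investigator and participant decide together about continuing drug after lower-grade adverse events (section 8.3.5), the examining clinician grades causality (section 8.3.3.2), and investigators may end participation (section 7.2). Knowledge of the emerging difference could colour any of these. Section 6.1.1 already concedes that patient blinding is imperfect, so there is little masking to spare.

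**Working it through.** **1. The plan's sample size.** Inputs from section 9.2: difference 5, SD 6.5, two-sided 0.05, power 80%, attrition 20%.

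- Normal approximation: n per group = 2 × (1.96 + 0.84)² × 6.5² / 5² ≈ 26.5, so 27.
- Two-sample t-test: 27.5, so 28 per group and 56 in total. Power at 28 per group is 80.7%.
- Enrolment: 56 / (1 − 0.20) = 70.

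The stated 28, 56 and 70 reproduce.

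**2. Where the look falls.** 0.5 × 70 = 35 enrolled, or 0.5 × 56 = 28 completers. The section does not say which total it means, and being accrued is not the same as having a week-8 outcome. Either way, about half the sample follows the look if the trial continues.

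**3. Participants on treatment at the look.** Section 5.5 expects 2 to 3 enrolled per month, and treatment lasts 8 weeks, about 2 months: 2 × 2 = 4 to 3 × 2 = 6. If the look is taken as soon as 35 are enrolled, these come on top of the 35 still to enrol (39 to 41 of 70). If it waits for the first 35 to reach week 8 while enrolment goes on, they are among the later 35.

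**4. The roles in section 9.4.6, side by side.**

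| Step | Who | DSMC's part |
|---|---|---|
| Run the interim analysis | Biostatistician; independence not stated | None stated |
| Review the data, decide on accrual | Named party, role not given | None stated |
| Stop for adverse events, any time | Research team and DSMC jointly | Agrees |
| Notify a termination | Named party | Informed within 48 hours |

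The table shows two routes to a stop, one with DSMC concurrence and one with notice only. The section does not say how they relate.

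**5. What follows by inference.** That the reviewer is not the DSMC is the natural reading: the accrual decision is given to a named party, and a termination is then reported to the DSMC as already decided. That the reviewer learns the between-group result is also likely, because both stopping rules are comparative and the safety rule identifies the arm. The text states neither outright.

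**6. Against the masking commitments.** Sections 6.3 and 8.1 withhold toxicology from the team because it could reveal allocation. Section 9.4.6 sets no comparable limit on who sees the comparison of pain, opioid use and serious adverse events. These passages sit badly together and need reconciling.

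**The case against.** A reader might infer several stronger things. The documents do not support them.

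- **That the mask is broken.** Section 6.3 promises that individual allocation stays unknown. Aggregate differences show a trend, not who takes what, and toxicology remains protected. The supported concern is a risk of operational bias, and only if the trial continues.
- **That the principal investigator, or someone at the top of the study team, reviews results by arm.** The name is removed and no role is given. Two removed names in one section need not be the same person, and section 10.1.5 provides for a medical monitor. The data to be reviewed are described only as pertinent, not as labelled by arm. The removal of the name is no defect.
- **That the DSMC only ever hears afterwards.** The 48-hour notice concerns termination. On the adverse-event route the DSMC must agree before the stop.
- **That the team must see adverse events by arm.** An unacceptable type or frequency can be judged on pooled, masked data.
- **That the DSMC cannot act alone.** The wording permits a joint decision without saying it is the only route. Sections 10.1.2 and 10.1.6, where its remit might stand, are headings only in this text.

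Nor do the documents show that the interim reviewer is one of the clinicians who agree doses or grade causality, so the path from knowledge to bias is possible but not established. The count of later participants would be the same for any half-way look and does not measure bias.

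What the objection leaves standing is the allocation of the decision. The protocol assigns it, and not to the DSMC. A statistical analysis plan could not change that without contradicting section 9.4.6.

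**Conclusion.** The concern holds in this form: section 9.4.6 places the interim data review and the decision on accrual with a named party, apparently not the DSMC. It gives the DSMC no review of the efficacy comparison, and it does not keep comparative results from a team that is otherwise masked. If the trial continues past the look, about half the sample (35 of 70 enrolled, or 28 of 56 completers) is exposed to a risk of operational bias.

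This rests on two readings: that the reviewer is not the DSMC, and that applying comparative rules means seeing comparative results. No shift in the endpoint or the error rate can be computed from the documents, and none is claimed. The change is a cheap improvement, to be made before the look because knowledge of interim results cannot be taken back.

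**What to change.** Rewrite section 9.4.6 as follows:

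- An unmasked statistician with no participant contact prepares the comparative interim report and sends it to the DSMC only.
- The DSMC reviews it and recommends that the study continue, be modified or stop.
- The investigator and study team receive that recommendation and nothing else from the report.
- To reconcile the two decision routes, state that the DSMC may recommend stopping the study on its own initiative.
- Replace the sentence giving the data review and accrual decision to a named party, and cross-refer to section 6.3.

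The cost is protocol wording, a short closed-report template and a statistician kept apart from participants. The DSMC already receives reports every 6 months. The one downside is that the investigator gives up sight of interim results.
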